3.6 FOLLOW-UP

Subjects will be enrolled over a period of two years and followed for five or six years.

Follow-up visits will be scheduled with broad time windows (see Chapter 4) as follows: monthly intervals for the first 3 months and every 3 months for the remainder of the study.

Testing for diabetes and the secondary endpoints will be performed yearly during the treatment period with no interruption of treatment. The goal is to study the effects of the treatments as carried out continuously. It could be argued, however, that a treatment might be effective in controlling diabetes so that it cannot be diagnosed by OGTT, as opposed to preventing the disease. We do not believe this represents a major problem in interpretation because even very effective therapy of type 2 diabetes rarely results in normalization of the OGTT. Furthermore, we would consider suppression of diabetes to the point of undectability (and/or prevention of the secondary endpoints) to be successful effects of the treatments, even while the treatments were continued.

The question of control vs. prevention will be further considered in those who survive the full treatment period without developing diabetes. These subjects will be followed for the development or appearance of diabetes for an additional six months after termination of all active treatment.

The variables to be measured at follow-up are described in Chapter 5, and the endpoints to be monitored are described in Chapter 7.

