It was not determined in this cross‑sectional study whether the differences in insulin secretion and action were results of physical training or of other differences between physically active and sedentary persons. Further studies demonstrated that plasma insulin concentrations decreased in obese, insulin‑resistant subjects who participated in physical‑training programs, even when they had no change in body composition or oral‑glucose tolerance (Björntorp et al 1973). Subsequently, numerous investigators have demonstrated that both regular physical training and the actual activity of exercise increase insulin sensitivity, whereas deconditioning and physical inactivity are both associated with the development of insulin resistance (Horton 1986). The effects of physical training on insulin sensitivity are rather short‑ lived, however, and they mostly disappear within a few days of the discontinuation of regular exercise (Burstein et al 1985). Marked reductions were detected in a group of Australia Aboriginal subjects who reverted from living a modern to a traditional life‑style which involved changes in physical activity, as well as in diet (O'Dea 1984). In the Swedish study (Eriksson and Lindgarde 1991) 10‑14 % increase was observed in oxygen uptake for both diabetic and IGT groups who participated in the program over their baseline values. This was in contrast to the control groups in which a reduction of 5‑9 % was observed. Body weight increased by 0.5‑1.7 % in the control groups, whereas it was reduced by 2.3.‑3.7 % in the active intervention groups. Glucose tolerance became normal in more than 50 % of the intervention group, with the cumulative incidence of diabetes being 10.6 % in the IGT group after 6 years. Blood pressure, lipids, and hyperinsulinemia were also reduced. Mortality in the intervention groups was 33 % lower than that in the control group.

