3.8 SAMPLE SIZE AND ENROLLMENT GOAL

We begin sample size determination by estimating the 5-year incidence of diabetes in the untreated persons with IGT to be 28% (see Chapter 2). Because of the uncertainty in the data needed to make this estimate, this figure may be an underestimate of the incidence of diabetes. If so, the power of the study would be greater than the following computations indicate. We are designing the study to be large enough to be able to detect, with 80% power (beta = 20%) at the 2-tailed 5% significance level (alpha = 5%), a 30% reduction in diabetes incidence due to diet-exercise treatment, ie, a reduction from 28% to 19.6%.

The possibility of a reduction in diabetes incidence by at least 30% is suggested by the results of the Malmöhus study (Sartor, et al, 1980) analyzed in accordance with randomized treatment assignment and by the nonrandomized treatment study of Eriksson and Lindgärde (1991). We are assuming that noncompliance in the DPS will be no worse than in these previous studies; therefore we are making no further adjustment for noncompliance. We will, however incorporate an adjustment for losses to follow-up, including deaths.

Letting p1 and p2 denote, respectively, the proportion of events (incidence of diabetes) in the control and treated groups, respectively, then, according to Halperin, et al (1968), the sample size required in each of the two groups is

N = {Zα[2p(1 - p)]1/2 + Zß[p1(1 - p1) + p2(1 - p2)]1/2}2 / [p1 -p2]2,

where p = (p1 + p2)/2 and Zα and Zß are the normal deviates associated with α and ß. With p1 = .28, p2 = .175, α (2-tailed) = .05, and ß = .20, the total minimum required sample size becomes

2N = 500.

In Malmöhus County from 1962-87, the mortality rate among persons aged 45-64 with IGT by WHO criteria was 19/1000 persons per year (Knowler, et al, in preparation), yielding an estimated 5.5-year cumulatie mortality rate of 10% in study participants. Allowing for 10% losses to follow-up from deaths over a 5.5-year period increases the sample size to

2N = 500/(1 - .10) = 556, or approximately 560.

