5.5 POST-STUDY FOLLOW-UP

All active treatments will cease at the end of 6 years (for those randomized in the first year of the study) or 5 years (for those randomized in the second year). The treatment will conclude with the usual annual examination (including an OGTT, Section 5.4). Thereafter, the reinforcement for the intensive diet-exercise program will be discontinued, although the patients assigned to this treatment will not be discouraged from continuing it on their own. All subjects who have not already reached the diabetes endpoint will be retested by OGTT three months and six months after termination of treatment. If one of these OGGTs indicates diabetes, the test will be repeated for confirmation of the diagnosis as described in Section 6.4.2. Following the six month OGTT, all procedures as specified by this protocol terminate, and further advice to subjects will depend on the outcome of the study.

CHAPTER 6. TREATMENT AND TESTING PROCEDURES

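### The six-month post-treatment phase tests control versus prevention only in diabetes-free completers who may keep up the programme, so neither a missing rebound nor a small excess supports the reading it invites

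*Protocol*

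**What the plan says.** Protocol Section 3.6 raises the objection that treatment might hold glucose down enough to hide diabetes from the OGTT without preventing it. It gives two answers: even very effective therapy rarely normalizes the OGTT, and suppression to the point of being undetectable would count as success. It then adds a further step: "The question of control vs. prevention will be further considered in those who survive the full treatment period without developing diabetes". Those subjects are followed for six more months, described as following the end of all active treatment.

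Section 5.5 sets out the mechanics: "All subjects who have not already reached the diabetes endpoint will be retested by OGTT three months and six months after termination of treatment". Reinforcement of the intensive programme stops, "although the patients assigned to this treatment will not be discouraged from continuing it on their own".

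On how quickly a benefit might fade, Section 2.3.1 says of the effects of training on insulin sensitivity that "they mostly disappear within a few days of the discontinuation of regular exercise".

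Section 8.3.1 plans life-table cumulative incidence by treatment group in one-year intervals. Section 4.1 closes each subject at the 5th or 6th anniversary of randomization.

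**The concern.** There are two difficulties, and they push in opposite directions.

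- **Continuation.** A withdrawal test is informative only to the extent that treatment is withdrawn. Section 3.6 assumes that it is; Section 5.5 secures only the end of counselling. Subjects who keep up diet and exercise would keep any suppression, and the catch-up would not appear.
- **Selection after randomization.** Subjects free of diabetes at the end of treatment are not a randomized set. If the programme works, the standard arm has already lost more of its susceptible members. The special arm's survivors then convert somewhat faster once counselling stops, even with no masked diabetes at all.

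At stake is the reading of the protocol's only further empirical step on an objection that it raises itself: no rebound could be taken as proof of prevention, and a small excess as unmasking.

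**Working it through.** **The plan's own figure.** The post-treatment phase has no stated sample size or power. Section 3.8 does reproduce: "With p1 = .28, p2 = .175", two-sided alpha 0.05 and 80% power give 250 per arm, 2N = 500, and 500/0.90 = 556, rounded to 560. The target stated in the same section is 28% to 19.6%; that mismatch is a separate matter. Both values of p2 are used below.

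**Inputs.** From Section 3.8: 560 subjects (280 per arm, assuming equal allocation), 10% deaths, 28% five-year incidence in the standard arm. Assumed: constant off-treatment hazard, the share c of special-arm subjects who continue, and the degree of heterogeneity in risk.

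**1. Power to see a catch-up if the whole benefit is suppression**

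- Entering the phase with p2 = 0.196: standard 280 × 0.9 × 0.72 = 181; special 280 × 0.9 × 0.804 = 203.
- Masked cases in the special arm: 280 × 0.9 × (0.28 − 0.196) = 21, which is 10.4% of 203.
- Off-treatment hazard: −ln(0.72)/5 = 0.0657 per year. Six-month risk: 1 − exp(−0.0657/2) = 3.2%.
- Special-arm six-month incidence = 0.104 × (1 − c) + 0.896 × 0.032. This assumes that every masked case who stops converts within the six months.
- Power = Φ[(difference − 1.96 × SE0)/SE1], with SE0 pooled and SE1 unpooled.

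| Share continuing (c) | Special, six months | Standard | Power, p2 = 0.196 | Power, p2 = 0.175 |
|---|---|---|---|---|
| 0% | 13.3% | 3.2% | 95% | 99% |
| 25% | 10.7% | 3.2% | 82% | 92% |
| 50% | 8.1% | 3.2% | 53% | 67% |
| 75% | 5.5% | 3.2% | 19% | 25% |
| 100% | 2.9% | 3.2% | about nil | about nil |

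**2. Excess from selection alone, with no suppression**

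*Two equal-sized risk classes.* A common hazard ratio is chosen so that the special arm reaches 19.6% at five years. Afterwards both arms have the off-treatment hazards.

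| Standard-arm five-year risks | Hazard ratio | High-risk share of survivors (standard / special) | Six-month incidence (standard / special) | Excess |
|---|---|---|---|---|
| 18% / 38% | 0.657 | 43.1% / 45.4% | 3.13% / 3.19% | 0.1 points |
| 8% / 48% | 0.636 | 36.1% / 41.0% | 2.82% / 3.09% | 0.3 points |
| 0% / 56% | 0.606 | 30.6% / 37.8% | 2.41% / 2.98% | 0.6 points |

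*Gamma frailty with variance θ.* The ratio of hazards among survivors is [(1 − Fs)/(1 − Fc)]^θ. At 5.5 years Fc = 1 − 0.72^1.1 = 0.303. Fs = 0.303 × 0.70 = 0.212 for a 30% reduction, or 0.303 × 0.625 = 0.190 for 37.5%. The base is 0.788/0.697 = 1.13 or 0.810/0.697 = 1.16, so the ratio is 1.06 to 1.08 at θ = 0.5, 1.13 to 1.16 at θ = 1, and 1.28 to 1.35 at θ = 2.

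*Precision.* With equal hazards, about 5.7 to 6.3 standard and 6.4 to 7.1 special cases are expected in six months (with and without 10% deaths). The 95% interval for the rate ratio spans exp[1.96 × √(1/e1 + 1/e2)], a factor of 2.9 to 3.1 either way. A true excess of this size could not be told from none.

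**3. Cumulative incidence from randomization through +6 months**

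Standard: 1 − 0.72 × (1 − 0.032) = 30.3%. Special, under full suppression with p2 = 0.196: 1 − 0.804 × (1 − six-month incidence), which gives 30.3% at c = 0, 26.1% at c = 50% and 21.9% at c = 100%. This estimate keeps the randomized groups. It does not remove the effect of continuation.

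**The case against.** The strongest reply is that the phase carries little weight. Section 3.6 gives two other answers first and only considers the question further here. The phase is not among the purposes or endpoints in Section 3.1, and Chapter 8 attaches no test to it. Retesting only diabetes-free subjects is natural for a first-occurrence endpoint, and the protocol does not spell out a rate ratio among survivors. This stands, and it keeps the point minor.

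A reader might infer that the phase cannot separate suppression from prevention at all, or that an excess of any size is uninterpretable. The figures do not support that. With few continuing, a full-suppression rebound of about 13% against 3% far exceeds what selection produces under the models above. Section 2.3.1 does not settle the matter either: its remark concerns insulin sensitivity, not diabetes incidence, and it suggests that three and six months are long enough for those who do stop.

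It can also be said that Section 8.3.1 already provides cumulative incidence by arm. As written it does not reach this phase: it runs in one-year intervals, and Section 4.1 closes each subject at the 5th or 6th anniversary.

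Finally, the remedy does not cure continuation. That is correct, which is why the conclusion must be limited as well as the estimate changed.

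**Conclusion.** The point holds in limited form. Sections 3.6 and 5.5 disagree on whether active treatment has ended during the phase, and must be reconciled. A large special-arm rebound would be informative. Absence of one is not evidence of prevention: power against full suppression falls from about 95% to 53% and 19% as assumed continuation rises from 0 to 50% and 75%. A small excess is not evidence of unmasking: selection alone gives 0.1 to 0.6 percentage points, or a rate ratio of about 1.06 to 1.35 at frailty variance 0.5 to 2. The continuation shares, risk classes and frailty variances are assumptions; the protocol gives none of them.

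A reader might go on to doubt the trial's main result. Nothing here supports that: the primary endpoint is assessed during treatment and does not depend on this phase. Severity is minor; the change is a cheap improvement.

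**What to change.** In Sections 3.6 and 5.5:

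1. Reconcile the statement that all active treatment has ended with the statement that continuation is not discouraged.
2. Base the control-versus-prevention question on the cumulative incidence of diabetes from randomization through the +6-month OGTT, in all randomized subjects by assigned arm, adding confirmed cases at +3 and +6 months to those found during treatment.
3. Report post-treatment rates in diabetes-free completers as descriptive only.
4. Limit the conclusion to whether the effect persists after counselling ends.

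The cost is protocol wording and one more life-table estimate from OGTTs already scheduled. The price is a more modest claim from the post-treatment phase.

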3.7 MASKING

3.7.1 The diet-exercise intervention will be only partly masked. This assignment can obviously not be masked from the subjects or from those Clinical Center personnel who counsel the subjects on their diet or exercise programs. However, all laboratory personnel, including those performing the glucose tolerance test, and the Endpoints Committee (Chapter 8) will be masked.

3.8 SAMPLE SIZE AND ENROLLMENT GOAL

We begin sample size determination by estimating the 5-year incidence of diabetes in the untreated persons with IGT to be 28% (see Chapter 2). Because of the uncertainty in the data needed to make this estimate, this figure may be an underestimate of the incidence of diabetes. If so, the power of the study would be greater than the following computations indicate. We are designing the study to be large enough to be able to detect, with 80% power (beta = 20%) at the 2-tailed 5% significance level (alpha = 5%), a 30% reduction in diabetes incidence due to diet-exercise treatment, ie, a reduction from 28% to 19.6%.

The possibility of a reduction in diabetes incidence by at least 30% is suggested by the results of the Malmöhus study (Sartor, et al, 1980) analyzed in accordance with randomized treatment assignment and by the nonrandomized treatment study of Eriksson and Lindgärde (1991). We are assuming that noncompliance in the DPS will be no worse than in these previous studies; therefore we are making no further adjustment for noncompliance. We will, however incorporate an adjustment for losses to follow-up, including deaths.

Letting p1 and p2 denote, respectively, the proportion of events (incidence of diabetes) in the control and treated groups, respectively, then, according to Halperin, et al (1968), the sample size required in each of the two groups is

N = {Zα[2p(1 - p)]1/2 + Zß[p1(1 - p1) + p2(1 - p2)]1/2}2 / [p1 -p2]2,

where p = (p1 + p2)/2 and Zα and Zß are the normal deviates associated with α and ß. With p1 = .28, p2 = .175, α (2-tailed) = .05, and ß = .20, the total minimum required sample size becomes

2N = 500.

In Malmöhus County from 1962-87, the mortality rate among persons aged 45-64 with IGT by WHO criteria was 19/1000 persons per year (Knowler, et al, in preparation), yielding an estimated 5.5-year cumulatie mortality rate of 10% in study participants. Allowing for 10% losses to follow-up from deaths over a 5.5-year period increases the sample size to

2N = 500/(1 - .10) = 556, or approximately 560.

Because the prevalence of IGT in the study populations is not precisely known, the expected number of cases of IGT to be detected on screening can only be approximated and these estimates need to be confirmed in a pilot study. We are therefore specifying that the Clinical Centers should recruit a minimum of 560 subjects. In that the promise of an intervention program may be used in motivating recruitment, each center may recruit more than its minimum goal. Any total larger than 560 will serve to increase the study's power.

To study serial changes in carotic artery diameter and thickness of the intima and media by B-mode ultrasound much smaller sample size would be sufficient, because these ultrasound measurements are based on continuous variables and because the measurement variability is relatively low (Bond et al 1991). However, this proposed sample size is too small to be able to detect possible differences in the incidence of acute CHD and stroke events between the groups. On the other hand, these acute CVD events can be pooled with the findings from the ultrasound measurements of carotic arteries when assessing the rate of worsening of atherosclerosis.

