As the incidence rates are in general higher in non-Causasian populations, the incidence has been estimated in Caucasians from the three studies in middle-aged Caucasians using WHO criteria: Malmöhus, Malmö, and San Antonio. If the 5-year cumulative incidence rates in these three studies are averaged, weighted by sample size (excluding the treated subjects in Malmö), the estimated 5-year incidence rate for Caucasians is 16%. For our study this is an underestimate because of the additonal entry criteria of obesity, which is associated with higher incidence of diabetes in persons with IGT at baseline (Saad, et al, 1988; Haffner, et al, 1990), and because some of the subjects will be followed for six, rather than five, years (depending on time of enrollment).

Most of these estimates are based on follow-up of persons with IGT diagnosed by one OGTT without corroborative evidence. Some corroborative evidence would be highly desirable before udertaking a long-term intervention in IGT. One possibility is to repeat the OGTT after a short interval of time and enroll only those persons meeting WHO criteria for IGT on both occasions. Another possibility would be to use HbA1c as an entry criteria. Among Pima Indians with IGT, those in the top 30% of the distribution of HbA1c had 2.47 times the incidence of diabetes during follow-up as did those in the lower 70%, or 1.74 times the incidence as in all the subjects with IGT combined (Little et al, submitted).

Although we are unaware of estimates of the multiplier of 1.74 for the incidence of diabetes in IGT diagnosed with repeated OGTTs, we will use this number to estimate the 5-year incidence of diabetes to be 1.74 times 16% = 28% in persons to be enrolled in the clinical trial.

2.2.3 Previous intervention studies in IGT. There have been few attempts to determine the effect of intervention on IGT.  Clinical research studies have shown that the administration of a hypocaloric diet to obese subjects with IGT leads to an improvement in glucose tolerance and, possibly, insulin action.  Similarly, sulphonyl­ureas can both increase insulin secretion and reduce insulin resistance in subjects with IGT or type 2 diabetes, and biguanide drugs reduce hyperglycemia by improving peripheral insulin action and inhibiting intestinal glucose absorption (see below, section 2.3.1).  There have been only a few attempts to examine the effects of diet on the incidence of diabetes in population samples.

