Malmö, Sweden. Eriksson and Lindgärde (1991) have recently completed a study of the feasibility of diet and exercise treatment of men with IGT in Malmö, Sweden. On the basis of population screening of 47-49 year old men, 217 subjects with IGT were identified. The criteria for IGT were similar to those proposed in the present study: the subjects had fasting blood glucose < 6.7 mM and two-hour blood glucose between 7.0 and 11.0 mM on two tests on two different days. The subjects were divided into two groups, 161 were treated with diet and exercise and 56 were a reference group. The groups were not assigned at random. The reference group were men referred to other clinics for specialized care, such as for hypertension or hyperlipidemia, and the remainder were treated by the investigators. The reference group were treated for their other medical conditions according to standard practice, but were not given specific treatment for hyperglycemia. The treated group were given dietary advice to reduce sugar and fat, increase complex carbohydrate and fiber, and lose weight if they were overweight. They were also trained in physical exercise by means of group exercise sessions for one hour, twice per week for the initial 6-12 months. Thereafter they were encouraged to continue exercising at home or in sports clubs. They were given no drug treatment for hyperglycemia, although some took drugs for other indications, e.g. hypertension. The treated subjects, but not the reference group, had a significant weight loss, most of which was maintained for 5 years. By the end of the 5-year treatment period, 11% of the treated subjects and 21% of the reference group had developed diabetes according to WHO criteria. Thus the incidence in the treated group was 0.5 times (95% confidence interval=0.3 to 1.0) that of the reference group. **This study is important in demonstrating the feasibility of carrying out a diet-exercise program for 5 years, and it suggests that the incidence of diabetes can be reduced by 50% by such treatment. A treatment effect was not definitely established, however, because the treatments were not assigned at random.**

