6.1 DIET-EXERCISE TREATMENT

Combined diet-exercise treatment will be compared to standard diet-exercise group. The groups will differ in several respects, including diet, physical activity, and weight loss.  Their comparison is intended to provide evidence as to which compo­nents affect the endpoint, but the main question is whether the combined treatment regimen is effective.

6.1.1 Standard diet-exercise treatment group. Subjects will be advised at entry to the trial by the dietitian to consume a diet with <30% of calories derived from fat, and to reduce alcohol and tobacco consumption to whatever extent possible.  Subjects should be advised to consume at least 15% of the daily calories at breakfast (defined as a meal taken within two hours of arising). Subjects will be advised to adjust total calories with the goal of weight loss to achieve body mass index <25 kg/m2.

These dietary goals will be implemented only by verbal or written instructions from a dietitian at the enrollment and annual visits.  None of the additional measures described below will be used.

6.1.2 Special diet-exercise treatment group.

(1) Subjects will be advised by the dietitian to consume a diet with 50% of calories derived from carbohydrate, 30-35% from fat (10 E% saturated fat, 20 E% unsaturated fat), cholesterol <300 mg/day, and 0.8 g protein/kg body weight/day. Dietary fiber will be increased to 30 g/day, or more if tolerated. This goal may be achieved through use of natural high fiber foods and by supplementation by soluble fibers such as beet fiber (Hagander, et al, 1988b). The caloric content of any supplemental fibers will be taken into account in the total caloric content of the diet. If subjects do not tolerate this much dietary fiber, the amount should be reduced to a tolerable level rather than withdrawing the subject from the diet treatment. Subjects will be advised to consume at least 10% of the daily calories at breakfast. Subjects will be encouraged to reduce alcohol and tobacco consumption.

(2) Intensive weight loss advice should be provided aiming to reduce body mass index to <25 kg/m2. If the subject does not succeed to lose weight during the first 6 months of the study and if his body mass index is >30, then VLCD (very low calorie diet) treatment may be used.

(3) Subjects will receive frequent regular dietary advice (see Table 4.1 for scheduled visits to the dietitian).

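### Section 3.8 uses an untreated-population rate of 28% for a control arm that gets dietitian advice, so the 80% power is not supported for special versus standard advice

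*Protocol*

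**What the plan says.** **Planning rate.** Section 3.8 opens by "estimating the 5-year incidence of diabetes in the untreated persons with IGT to be 28" percent. Section 2.2.2 derives this as 1.74 × 16%. The 16% is a weighted average of three studies in middle-aged Caucasians using WHO criteria, "excluding the treated subjects in Malmö".

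**Use as the control rate.** Section 3.8 continues: "Letting p1 and p2 denote, respectively, the proportion of events (incidence of diabetes) in the control and treated groups". The inputs are "With p1 = .28, p2 = .175, α (2-tailed) = .05, and ß = .20", which give 2N = 500, and 556 (about 560) after 10% losses. The effect in words is different: "a 30% reduction in diabetes incidence due to diet-exercise treatment, ie, a reduction from 28% to 19.6" percent.

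**Actual control arm.** Under section 6.1.1 a dietitian advises the standard group to limit fat to under 30% of calories and to cut alcohol and tobacco. On weight: "Subjects will be advised to adjust total calories with the goal of weight loss to achieve body mass index <25 kg/m2". Section 6.1.2 sets the same BMI goal for the special group. Section 6.1.1 places the control advice at enrollment and annual visits; a note to Table 4.1 says enrollment only.

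**Allowances made.** Section 3.8 adjusts for losses to follow-up, declines a further adjustment for noncompliance, and does not mention an effect of the standard advice. It says only that 28% may be too low, in which case power would be greater. Section 8.4 expects the standard group to show the natural history of IGT.

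**The concern.** If fat and weight-loss advice has any effect, it lowers control incidence below that of the cohorts behind the 28%. The power then falls, moderately if the special program keeps its relative advantage over the advised controls, and steeply if that advantage was really measured against no treatment.

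The second possibility cannot be set aside. One of the two studies cited for the effect size, the Malmö study, compared diet and exercise with a reference group who were treated for other conditions "but were not given specific treatment for hyperglycemia".

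The interpretation of a null result is at stake. A reader who trusts the 80% could take it as evidence that diet-exercise treatment does not work, when the trial compared two levels of advice with unknown power.

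**Working it through.** **Inputs.** Control p1 = 0.28, special p2 = 0.175, two-sided alpha 0.05 (Zα = 1.96), power 80% (Zß = 0.8416), equal groups, all from section 3.8. Untreated 5-year rates come from Table 2.1.

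**1. Source of the 28%.** The untreated WHO-criteria rows are Malmöhus 16% (n = 22), Malmö 21% (n = 56) and San Antonio 12% (n = 61). Weighted mean: (16×22 + 21×56 + 12×61)/139 = 2260/139 = 16.3%. Then 1.74 × 16% = 27.8%, or 28%. The base consists of untreated subjects only.

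**2. The plan's sample size.** The formula in section 3.8 gives "the sample size required in each of the two groups is"

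N = {Zα√[2p(1−p)] + Zß√[p1(1−p1) + p2(1−p2)]}² / (p1−p2)², with p = (0.28 + 0.175)/2 = 0.2275.

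N = (1.96×0.5929 + 0.8416×0.5882)² / 0.105² = (1.162 + 0.495)² / 0.011025 ≈ 249.05, rounded up to 250. So 2N = 500, and 500/0.9 = 556. Both stated figures reproduce.

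**3. Power at 250 per group.** Solving the same formula for power:

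Power = Φ{[√n (p1−p2) − Zα√(2p(1−p))] / √[p1(1−p1) + p2(1−p2)]}.

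For 0.28 versus 0.175 this is 80.2%.

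**4. If the standard advice lowers control incidence by a fraction r.** The value of r is an assumption; the documents give none. Control rate = 0.28(1−r).

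| r | Control rate | 37.5% relative reduction kept | Special arm fixed at 17.5% |
|---|---|---|---|
| 0 | 28.0% | 80.2% | 80.2% |
| 5% | 26.6% | 77.5% | 69.0% |
| 10% | 25.2% | 74.6% | 55.6% |
| 15% | 23.8% | 71.6% | 41.3% |
| 20% | 22.4% | 68.3% | 27.8% |

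The 37.5% is 1 − 0.175/0.28. The last column is the worst case: only the controls improve on the planning rates.

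**5. The opposite direction.** The 28% is a 5-year rate, and the Summary gives a mean duration of 5.5 years. Linear extension, the method used in Table 2.1, gives 28% × 5.5/5 = 30.8%. Since 28/30.8 = 0.909, an advice effect of about 9% brings the control rate back to 28%. With the 37.5% relative reduction kept, power is 82.4% at r = 5% (control 29.26%) and 79.6% at r = 10% (control 27.72%).

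This recovery depends on the relative reduction holding against advised controls. If the 37.5% applies against no treatment instead, the special arm is at 30.8% × 0.625 = 19.25%, and power against a 28% control rate is about 63%.

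**6. The effect stated in words.** For 0.28 versus 0.196, power at 250 per group is 59.7%, and 80% power needs 2N = 806 (896 after 10% losses). This gap exists with no advice effect at all and should not be attributed to the control arm.

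**The case against.** The control advice is slight. Section 6.1.1 limits it to verbal or written instructions and withholds the special group's additional measures, and section 5.1.2 does not count routine dietary advice as prior treatment. A near-zero effect is a legitimate planning assumption. Section 2.2.2 also gives reasons why the base rate may be low: the obesity criterion, and follow-up of six years for some. The follow-up reason alone could offset an advice effect of about 9%. These points stand. They make the assumption arguable, but section 3.8 does not state it.

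A reader might infer more than the documents support:

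- **That the whole planned contrast is treated versus untreated.** Section 3.8 also cites the Malmöhus study, in which, according to section 2.2.3, all randomized groups received diet treatment. That contrast tested tolbutamide (10% versus 13% at ten years), so it does not supply a special-versus-standard diet effect either. The Malmö study compared treatment with no specific treatment, but it was not randomized.
- **That Table 2.1 bounds the advice effect at 37.5%** (Malmöhus, WHO criteria, 32% untreated and 20% treated at ten years). The treated row may include tolbutamide. The counts are about 7/22 and 5/25: risk ratio 0.63, 95% CI 0.23 to 1.70, Fisher exact p = 0.50. These rows fix no bound.
- **That section 3.8 says the rate can only be too low.** It says that it may be.

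**Conclusion.** The mismatch is real. The 28% describes untreated cohorts, the control arm is advised, and section 3.8 neither allows for this nor says that it assumes no effect. The 80% is not supported for special versus standard advice.

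The size is conditional. For an assumed 5-20% lower control incidence and 250 evaluable per group, power is 78-68% with the 37.5% relative reduction kept and 69-28% with the special-arm rate held at 17.5%.

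The stronger conclusion, that the 80% is shown to be wrong or the trial shown to be underpowered for this reason, does not follow. It would require the advice effect to exceed the upward pressure from longer follow-up and obesity, and the documents quantify neither the advice effect nor the effect of the obesity criterion. Neither the size nor the net direction of the error is fixed. The shortfall for the 30% reduction stated in words, about 60% power, is a separate and firmer finding.

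**What to change.** In section 3.8:

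- State that 28% comes from untreated cohorts and is assumed to hold under the section 6.1.1 advice, with the reason for that assumption.
- Name the detectable effect as special versus standard advice.
- Give a short table of power at the planned size for control rates below and above 28% (for example 22.4% to 30.8%), saying whether the special-arm rate or the relative reduction is held fixed.
- Add to the remark that 28% may be too low that the standard advice may lower the control rate.
- Reconcile the 30% reduction in words with the 17.5% in the formula, and carry the result into the Summary.

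The counseling schedule for controls in section 6.1.1 and the note to Table 4.1 must also be reconciled, because the assumed control rate depends on it.

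The cost is some wording, one small table and a less favourable stated power. These changes call for no extra subjects.
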